### Data management, governance, and data access

The University of Oxford is the sponsor of this research. The study will comply with the General Data Protection Regulation (GDPR) and Data Protection Act 2018. The data management policy and governance framework can be found at https://www.condor-platform.org/condor_workstreams/raptor. Only substantive employees of the University of Oxford will have access to the data and only for the purposes described in the study protocol. Direct access will be granted to authorised representatives from the sponsor and host institution for monitoring and/or audit of the study to ensure compliance with regulations. The legal basis for the Oxford-RCGP RSC surveillance is that this is classified as Health Protection under Regulation 3 of The Health Service (Control of Patient Information) Regulations 2002 and approved annually by the Public Health England Caldicott Guardian; other studies require appropriate ethical approval.

### Dissemination and publication policy

We will publish the results in open-access journals, the protocol on the study website (https://www.condor-platform.org/condor_workstreams/raptor) and registries, and summary reports which can be made publicly available through, e.g. the websites of the study and of the NIHR Community Healthcare MIC (https://www.community.healthcare.mic.nihr.ac.uk/). We will work with patient and public representatives to ensure that such reports are communicated in an appropriate manner for a lay audience. The Investigators will be involved in reviewing drafts of the manuscripts, abstracts, press releases, and any other publications arising from the study. Authors will acknowledge that the study was funded by UKRI-MRC and any other funding that is secured. Authorship will be determined in accordance with the ICMJE guidelines and other contributors will be acknowledged.

## Discussion

There is a need for diagnostic accuracy studies in the community setting of POCTs for the detection of SARS-CoV-2. It is important to identify high-performing tests to prioritise these for use, and to avoid poorly performing technologies. We have set out in this protocol how we will achieve this in UK community settings. The RAPTOR-C19 diagnostic platform has been developed to support the UK’s Urgent Public Health response to COVID-19. Building RAPTOR-C19 on top of an established surveillance network (RCGP RSC) gives efficiencies, gives advantages for digital data collection, and aids recruitment.

### Strengths and limitations

The prevalence of SARS-CoV-2 in the tested population will be the primary determinant of the rate at which RAPTOR-C19 can evaluate the accuracy of each POCT. The UK had surpassed a peak of SARS-CoV-2 infections at the time this protocol was being prepared for publication, with national easing of lockdown underway. COVID-19 testing capacity in the NHS took time to develop, with initial testing mainly occurring in the hospital setting, later through local COVID-19 ‘hubs’ and then national testing centres. At the height of the first peak, the prevalence of infection was > 30% in those tested [38]. As testing increased outside of the hospital setting, the prevalence of SARS-CoV-2 infections fell, due to a combination of decreasing national SARS-CoV-2 infection prevalence and increased testing in a broader population [39]. Whilst we welcome this reduction in prevalence, it results in larger sample sizes for clinical research.

By recruiting symptomatic people who are clinically suspected to have SARS-CoV2 infection, RAPTOR-C19 will increase the likelihood of identifying positive cases in the community above the background prevalence. To maximise recruitment RAPTOR-C19 will recruit from a base of high-throughput practices, with large practice populations, and/or practices acting as COVID-19 hubs, with wide geographical spread throughout the UK, including urban centres with high population density. Additional practices will be asked to act as stand-by sites where evaluation may begin rapidly in response to local outbreaks of SARS-CoV-2. This combined approach is intended to increase the likelihood of capturing positive cases in symptomatic people above the background national prevalence of SARS-CoV-2. From a public health point of view, correctly ruling-in active SARS-CoV-2 is just as important as ruling it out. Therefore, we need POCTs that are both highly sensitive and highly specific. The CONDOR triage process aims to identify POCTs that align with the MHRA specification based on the available data from the manufacturer or independent analytical analyses. By starting with a rigorous selection process, we reduce the probability of evaluating poorly performing POCTs.

A strength of the RAPTOR-C19 protocol is the stopping criteria to identify POCTs that have already exceeded the maximum number of false positives or false negatives necessary to be able achieve the target sensitivity and specificity. A corresponding weakness is that a test which has focussed on achieving high sensitivity but has low specificity may be disadvantaged in a low prevalence setting, especially if the anticipated prevalence used to set the stopping criteria, was higher than the actual prevalence. In this circumstance, tests may be excluded from the analysis because of accumulating too many false positive results in comparison to the laboratory and composite reference standards. Nevertheless, these stopping criteria reflect MHRA mandated performance criteria. During early evaluations we will establish whether sufficient information to create the composite reference standard can be obtained sufficiently quickly to make stopping criteria viable.

We recognise the challenges of recruitment in a changing policy environment, with variable disease prevalence. GP sites will be recruited from the RCGP Research and Surveillance Centre (RSC) is an internationally renowned source of information, analysis, and interpretation of primary care data [40]. The dataset is nationally representative [41], having only small differences with the national population, which have now been quantified and can be assessed for clinical relevance for specific studies. With twice weekly data extractions, the dataset is one of the most up to date in the UK, and now a platform within ORCHID. ORCHID is in the process of enhancing the frequency of extraction and scope of data linkage. It is already extracting primary care computerised medical records (CMRs) daily and linking with linked hospital data and mortality data. ORCHID will additionally support RAPTOR-C19 by allowing patient follow-up within the RCGP RSC network, and the creation of an enhanced composite reference standard to overcome limitations of laboratory reference tests [30].

However, in the pandemic situation, community testing has been expanded in unexpected and unprecedented ways. In order to respond to the needs of the community and maximise recruitment and coverage of different clinical settings, we may also recruit from other community settings where reference RT-PCR swabs are being or can be collected. These might include national testing centres, home testing systems, surveillance and national telephone triage services, pop-up community laboratories in areas of increasing local prevalence, transport infrastructure and the UK borders, and educational or commercial organisations. People tested at these locations will not necessarily be registered at RCGP RSC practices, and the venues may not be able to undertake venepuncture, so it may not be possible to use the same reference standards as at GP practices. Many of these settings undertake service evaluations that align with government priorities, and we would seek to partner with these organisations. We would aim to establish data sharing agreements for a limited set of de-identified participant and test result data to permit the primary evaluation of POCTs used in these settings against the usual RT-PCR reference standard, and depending on the data they are able to collect, modified enhanced standards.

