### Number of participants

We have calculated sample sizes using standard methodology based on minimum clinically relevant sensitivity or specificity (whichever is the most critical for the intended placement in the care pathway), not expected values from preliminary work [16]. For example, acceptable thresholds for minimum sensitivity and specificity of 80% and 95% respectively, can be used to determine sample size requirements and a strategy for early identification of poorly performing tests.

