### Stopping criteria

Assuming a test with 90% sensitivity, a 99% specificity, and a pre-test probability (prevalence) of 30%, we would require 200 participants to meet the minimum thresholds as stated above. This would also mean that tests with more than seven false negatives or two false positives could be immediately dropped from the study. This allows us to exclude tests with sensitivities of 50%, 60%, 70%, or 80% after the first 50, 60, 80, and 120 participants recruited. For tests with poor specificities of 80%, 85%, 90%, or 95% these would be identified after 15, 20, 30, and 60 participants recruited. The prevalence of COVID-19 affects the sample size required. With a pre-test probability (prevalence) of 5% we would require 1200 participants to evaluate a POCT and interim futility analyses will stop the evaluation after seven false negatives or twelve false positives. POCTs with an actual sensitivity of 50%, 60%, 70%, or 80% would reach futility criteria after the first 280, 350, 470, and 700 participants. POCTs with an actual specificity of 80%, 85%, 90% or 95% would reach futility criteria after the first 65, 85, 130, and 255 recruited participants.

Evaluations of the first POCTs will be performed without implementation of stopping criteria to establish whether sufficient information to create the composite reference standard can be obtained sufficiently quickly to make these criteria viable. The figures presented here should therefore be regarded as indicative for a POCT designed to detect active infection and will be reviewed once this information becomes available.

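### The indicative stopping limits are fixed counts not tied to accrued reference-positives and reference-negatives, so the false-negative limit drops good tests when prevalence exceeds the anticipated value

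*Protocol article*

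**What the plan says.** Number of participants offers, as an example, "acceptable thresholds for minimum sensitivity and specificity of 80% and 95% respectively". Stopping criteria then works two cases.

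- **30% prevalence:** "Assuming a test with 90% sensitivity, a 99% specificity, and a pre-test probability (prevalence) of 30%, we would require 200 participants", and "tests with more than seven false negatives or two false positives could be immediately dropped from the study".
- **5% prevalence:** the planned size rises to 1200, where "interim futility analyses will stop the evaluation after seven false negatives or twelve false positives".

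The same section says that the first POCTs will be evaluated without stopping criteria. It calls the figures indicative, to be reviewed once it is known how quickly composite reference information can be obtained. Study end has the Study Management Committee review recruitment against current PHE prevalence data, because prevalence affects sample size. It does not mention the counts.

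Strengths and limitations concedes that a low-specificity test may be disadvantaged at low prevalence, "especially if the anticipated prevalence used to set the stopping criteria, was higher than the actual prevalence". It does not discuss the false-negative limit. It also describes hubs and outbreak stand-by sites meant to "increase the likelihood of capturing positive cases in symptomatic people above the background national prevalence".

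**The concern.** False negatives can arise only among reference-positives, and false positives only among reference-negatives. A fixed count is a statement about accuracy only once its denominator is known. The limits assume the denominators that follow from an anticipated prevalence, and the article gives no rule for what happens when the realised numbers differ.

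If prevalence runs above the anticipated value, positives accrue faster and a good test passes seven false negatives through volume alone. Its evaluation would then stop early although its accuracy is acceptable. The recruitment strategy seeks prevalence above the national background, so an anticipated value anchored on national data would tend to be too low.

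**Working it through.** **Inputs.** From Number of participants and Stopping criteria: minimum sensitivity 80% and specificity 95%; design test 90% / 99%; N = 200 at 30% (limits 7 FN, 2 FP); N = 1200 at 5% (limits 7 FN, 12 FP). The actual prevalences tried below (20–40% against the 30% plan, 3–10% against the 5% plan) are my assumptions.

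**The plan's own figures.** Expected positives are 200 × 0.30 = 60 and 1200 × 0.05 = 60; expected negatives are 140 and 1140.

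- With 60 positives, 7 FN gives a Wald 95% lower limit of 0.802 and 8 FN gives 0.781. The limit of seven therefore fits 60 positives and the 80% minimum.
- The FP limits are 1% of negatives rounded up: 1.4 to 2, and 11.4 to 12.
- The stated stopping times equal limit / [prevalence × (1 − sensitivity)] or limit / [(1 − prevalence) × (1 − specificity)]. For example, 7/(0.30 × 0.20) = 116.7 (stated 120), 7/(0.05 × 0.20) = 700 (stated 700) and 12/(0.95 × 0.05) = 252.6 (stated 255). All sixteen agree after rounding up.

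Prevalence is thus built into every figure, and the stopping times use the count itself (7, not 8).

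**False-negative limit at planned N.** FN ~ Binomial(N, prevalence × (1 − sensitivity)), and a test is dropped if FN > 7.

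| Plan | True sensitivity | Actual prevalence: probability dropped |
|---|---|---|
| N = 1200 | 90% | 5%: 26%; 7%: 60%; 10%: 91% |
| N = 1200 | 80% | 5%: 91%; 3%: 43% |
| N = 200 | 90% | 30%: 25%; 35%: 40%; 40%: 55% |
| N = 200 | 80% | 30%: 92%; 25%: 79%; 20%: 55% |

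At 10% prevalence, 1200 participants give about 120 positives. Eight FN is then 112/120 = 93.3%, with an exact 95% lower limit of 87.3%, well clear of 80%. Up to 15 FN would keep the exact lower limit at or above 80%. The rule would stop this test for futility although it meets the target.

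The convention matters too. If the evaluation stops at the seventh false negative, the 90%-sensitive test in the 1200 plan is dropped 39% of the time at 5% and 73% at 7%.

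**False-positive limit at planned N.** FP ~ Binomial(N, (1 − prevalence) × (1 − specificity)), with a 99%-specific test.

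- N = 200, dropped if FP > 2: 17% at 30% prevalence, 22% at 20%.
- N = 1200, dropped if FP > 12: 36% at 5%, 38% at 3%, 29% at 10%.

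**False-positive limit if N is extended to keep 60 positives but the limit stays at 2.** N = 60/prevalence, and negatives = N − 60.

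- 30%: N = 200, 140 negatives, dropped 17%.
- 20%: N = 300, 240 negatives, dropped 43%.
- 10%: N = 600, 540 negatives, dropped 91%.

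**The case against.** The strongest reply is that these are not operative rules. The thresholds are introduced as an example, the counts are indicative and due for review, and the first POCTs are exempt. That stands, and it lowers the severity. It does not remove the point: the stated trigger for review is how fast composite information arrives, so a review on that ground need not touch prevalence.

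Second, the Study Management Committee reviews recruitment against prevalence. If N is re-set to about 60 positives, seven false negatives stays calibrated and the 60% and 91% figures do not arise. Both worked examples do imply 60 positives, with the FP count moved from 2 to 12. This is fair, but the article speaks only of recruitment. Changing N without also changing the FP count moves the error to the false-positive side, as the last calculation shows.

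Third, a reader might infer that the limits hold only if prevalence is exactly as anticipated, or that poor tests would be accepted. The documents support neither. At fixed N the false-positive limit is fairly insensitive to a modest shift. A poor test that escapes early stopping is still reported with exact 95% confidence intervals, so the loss is efficiency, not a wrong final estimate.

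Fourth, the false-positive weakness is openly conceded. The false-negative side is not.

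**Conclusion.** The point holds as a should-fix. As written, the limits are absolute counts with no link to the accrued denominators, and the unacknowledged weakness is the false-negative limit when prevalence rises. Going from 5% to 7%, or from 30% to 40%, more than doubles the chance of dropping a 90%-sensitive test (26% to 60%; 25% to 55%). A fall from 30% to 20% cuts early removal of an 80%-sensitive test from 92% to 55%.

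These figures assume that N stays as planned, that participants are independent, that each test is judged against the reference standard as given, and that more than seven is the limit. Not all the dropping is due to prevalence: 25–26% occurs at the anticipated value. The FP limit in the 5% plan is also far tighter than the 95% minimum requires, since 42 false positives among 1140 negatives would still keep the exact lower limit at or above 95%, against a limit of 12.

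A must-fix rating would go too far, because no test can be dropped under these counts until stopping criteria are switched on.

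**What to change.** When the indicative counts are reviewed, and before stopping criteria are applied to any POCT:

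1. State each evaluation's target as numbers of reference-positives and reference-negatives, not participants.
2. Index the FN limit to positives and the FP limit to negatives. Stop when the 80% or 95% minimum can no longer be met at the planned final number of that group, and name the interval method. The choice matters: with 60 positives the Wald interval allows 7 FN and the exact interval 5. With the exact interval, 40, 60, 80 and 120 positives allow 2, 5, 8 and 15 FN.
3. Use one convention throughout, either stopping at the limit or on exceeding it, and recompute the stopping times to match.
4. Extend the limitation in the discussion to the false-negative side.

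The cost is a rewording of Stopping criteria and one look-up table. No procedures are added. Total recruitment would vary with prevalence, which Study end already anticipates.

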### Future research

The development of the RAPTOR-C19 platform opens the door to future evaluations of POCTs for other infectious diseases in the community alongside or instead of COVID-19 POCTs. The underlying digital infrastructure of ORCHID provides a rich retrospective linked primary care EHR dataset upon which to build future prospective analyses of POCTs for communicable and non-communicable diseases, such as biomarkers for cancer diagnosis or cardiovascular disease monitoring. The rapid growth of the RCGP RSC to support priority COVID-19 research, such as the PRINCIPLE trial, has created the largest network of GP sites available for interventional and diagnostic research in the UK.

### Conclusion

We have described the protocol for a diagnostic accuracy platform for SARS-CoV-2 POCTs specific to community settings. It leverages existing surveillance, digital, and primary care infrastructure and aims to identify POCTs that meet government specified diagnostic performance levels.

## Data Availability

Not applicable.

## Abbreviations

CMRs: Computerised medical records
CONDOR: COVID-19 National DiagnOstic Research and Evaluation Platform
COVID-19: Coronavirus 2019 disease
CRN: Clinical Research Network
eCRF: Electronic case report form
EHR: Electronic health record
FN: False negative
FP: False positive
GCP: Good clinical practice
GDPR: General Data Protection Regulation
GP: General practitioner
HRA: Health Research Authority
ICMJE: International Committee of Medical Journal Editors
IgG: Immunoglobulin G
MIC: NIHR Community Healthcare MedTech and In vitro Diagnostics Co-operative
NHS: National Health Service
NIHR: National Institute for Health Research
OP/NP: Oropharyngeal/nasopharyngeal
ORCHID: Oxford Royal College of General Practitioners Clinical Informatics Hub
PC: Primary care
PHE: Public Health England
POCT: Point-of-care test
RAPTOR-C19: RApid community Point-of-care Testing fOR COVID-19
RCGP RSC: Royal College of General Practitioners Research and Surveillance Network
REC: Research ethics committee
RT-PCR: Real-time polymerase chain reaction
SAP: Statistical analysis plan
SARS-CoV-2: Severe Acute Respiratory Syndrome Coronavirus 2
STARD: Standards for Reporting Diagnostic Accuracy Studies
